### Participants

#### Number of patients needed

We plan to divide the patients into the obstructive jaundice group (total bilirubin (TBL) value > 17.1 μmol/L) and the control group (TBL < 17.1 μmol/L) based on their diagnosis and TBL value. The primary endpoint is the difference in the requirement of remimazolam.

The group sample size was calculated based on the differences in remimazolam requirement to reach BIS value ≤ 50 longer than 5 s in our previous study, in which the mean remimazolam requirement was 0.13 ± 0.04 mg/kg (*n* = 6) in the obstructive jaundice group and 0.16 ± 0.04 mg/kg (*n* = 6) in the non-obstructive jaundice group, The following formula: *n* = 15.7/ES^2^ + 1, where ES = effect size = (difference between the groups)/(mean of the SD between the groups), with *α* = 0.05 and power = 0.8, was used to determine that the study would be adequately powered with *n* = 29 per group. Considering a dropout rate of 10%, the estimated sample size will be at least 32 patients per group; thus, a total of 64 patients will be needed.

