### Allocation and allocation concealment

Patients are allocated to the obstructive jaundice group or the control group based on the TBL values after they sign the informed consent form. Because obstructive jaundice is easy to distinguish from the appearance of skin color, it is difficult to double-blind. However, the anesthesiologist assistant is blind to the grouping or induction method but only records the data through a local area network (LAN) in the next room.

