### Intervention

After 8 h of fasting, the patients without premedication will be brought into a quiet operating room where a cannula was inserted into the right internal jugular vein under local anesthesia for infusion of remimazolam and liquid. Radial artery catheterization was placed to measure invasive arterial blood pressure. Heart rate (HR), invasive blood pressure (IBP), electrocardiogram (ECG), end-tidal carbon dioxide (ETCO_2_), and oxyhemoglobin saturation (SpO_2_) are routinely monitored during the whole process of research (Philips HP Viridia24/26 M1205A). Apply the BIS sensor (BIS™XP sensor) as recommended by the manufacturer. The patients are asked to keep their eyes closed and covered with gauze to avoid any interference with sound and light stimulation. The temperature of the room is controlled at 23 °C.

The study is designed to record the remimazolam requirement with BIS of 50 as the endpoint. The patients will be treated with remimazolam at a rate of 6 mg/kg/h by a Graseby 3500 syringe pump (SIMS Graseby Ltd., Herts, UK) until the BIS is ≤ 50 longer than 5 s. The assistant anesthesiologist, who is not aware of the study group, observes the vital signs and BIS values in the next room via the LAN, determines the endpoint of titration, and records the dosage of remimazolam used and the time interval between the start and end of the infusion. Then, the patients will be given 0.4–0.6 μg/kg sufentanil and 0.2 mg/kg cisatracurium, and endotracheal intubation will be performed 3 min later for anesthesia induction. Anesthesia is maintained with sevoflurane (1.5–2.5%) at an appropriate standard for surgical procedures. Hemodynamic data are collected and recorded at relevant points during the peri-intubation period.

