### Data collection and data management

Before surgery, general information and the surgical methods of the patients are investigated, and indexes such as TBL, bile acid, albumin, alanine aminotransferase (ALT), aspartate aminotransferase (AST), and alkaline phosphatase (ALP) are recorded. The requirement of remimazolam until the patient’s BIS value reaches 50 and the time interval from the start to the end of infusion are recorded. Pulmonary and cardiovascular vital signs are recorded electronically throughout the procedure, including SpO_2_ measured by a pulse oximeter, HR, IBP, RR, and ETCO_2_. Data will be collected on paper case report forms (CRFs) by an anesthesiologist assistant blinded to the group allocation in each center.

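### The recorded primary dose is most naturally the dose to pump stop, so a call-to-stop time that differs by group would enter an effect worth only 18 s of infusion

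*Protocol article*

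**What the plan says.** All references are to the Protocol article.

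- **Intervention.** Remimazolam runs at 6 mg/kg/h until BIS has been at or below 50 for more than 5 s. An assistant who does not know the group follows BIS from the next room over the LAN and "determines the endpoint of titration, and records the dosage of remimazolam used and the time interval between the start and end of the infusion".
- **Assessment of primary endpoint.** This repeats that the requirement and the start-to-end infusion time are recorded.
- **Data collection and data management.** Here the requirement is described as running until BIS gets to 50, with no 5 s condition, and the infusion time is listed separately. The same section says that "Pulmonary and cardiovascular vital signs are recorded electronically throughout the procedure" and names SpO2, HR, IBP, RR and ETCO2. BIS is not named. The blinded assistant at each center completes paper case report forms.
- **Allocation and allocation concealment.** "Because obstructive jaundice is easy to distinguish from the appearance of skin color, it is difficult to double-blind". The remedy offered is the blinded assistant in the next room.
- **Number of patients needed.** The trial is sized on an earlier study with 6 patients per group and the same 5 s BIS criterion: "the mean remimazolam requirement was 0.13 ± 0.04 mg/kg" "in the obstructive jaundice group and 0.16 ± 0.04 mg/kg" in the non-jaundiced group.

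**The concern.** Two events end the titration. The assistant judges that the criterion has been met, and the infusion then stops. If the recorded dose runs to the second event, every second between the two is counted as drug requirement.

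Blinding protects the first event. It does not clearly protect the second. The patient and the infusion are in the operating room, the caller is in the next room, and the article describes the LAN only as a means of observing and recording. It does not say how the call reaches the pump or who stops it. Staff beside the patient can see jaundice. The Discussion also reports the team's earlier findings of greater anesthetic sensitivity, and more bradycardia and hypotension, in jaundiced patients. Quicker stopping in jaundiced patients would lower their recorded dose and so favor the trial's hypothesis.

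A few seconds matter only if the planned effect is itself short when expressed as infusion time. The working below checks this.

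**Working it through.** **1. The plan's own figure.** The inputs from Number of patients needed are means of 0.13 and 0.16 mg/kg and an SD of 0.04 mg/kg in each group, "with *α* = 0.05 and power = 0.8".

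- Effect size = (0.16 − 0.13)/0.04 = 0.75.
- n = 15.7/0.75² + 1 = 28.9, so 29 per group, as stated. An exact two-sided t test with 29 per group has power 0.80.
- With the 10% allowance, 29 × 1.10 = 31.9, which gives the stated "at least 32 patients per group; thus, a total of 64 patients will be needed".

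The figure is reproduced.

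**2. The effect in seconds.** The infusion rate from Intervention is 6 mg/kg/h ÷ 3600 = 0.00167 mg/kg per second.

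- Jaundice group mean: 0.13/0.00167 = 78 s.
- Control group mean: 0.16/0.00167 = 96 s.
- Planned difference: 0.03/0.00167 = 18 s.
- SD: 0.04/0.00167 = 24 s.

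One second of infusion is therefore 5.6% of the planned difference.

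**3. A delay common to both groups.** If each group's mean rises by the same d, then (0.16 + d) − (0.13 + d) = 0.03. The comparison is unchanged.

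**4. A delay that differs by group.** The article gives no delays, so the seconds below are assumptions. Dose = seconds × 0.00167. The rejection rates and power are for a two-sided t test with 29 per group and noncentrality = difference/(0.04 × √(2/29)) = difference/0.0105.

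| Assumed group difference in call-to-stop time | Dose (mg/kg) | Share of 0.03 | Rejection rate with no true difference | Power if the delay works against a true 0.03 |
|---|---|---|---|---|
| 2 s | 0.0033 | 11% | 6.1% | 0.70 |
| 3 s | 0.0050 | 17% | 7.5% | 0.65 |
| 5 s | 0.0083 | 28% | 12.2% | 0.53 |
| 10 s | 0.0167 | 56% | 34.5% | 0.24 |

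If the delay instead works with the effect (jaundiced patients stopped sooner), the expected observed difference for 3, 5 and 10 s is 0.03 plus the dose in the table: 0.035, 0.038 and 0.047 mg/kg.

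**5. A purely random delay.** If it is not already in the SD, the total SD is √(0.04² + (s × 0.00167)²), where s is the SD of the delay in seconds. For s = 2, 5, 10 and 15 s the plan's formula gives 30, 31, 34 and 40 per group, and power at 29 per group is 0.80, 0.79, 0.74 and 0.66. These are upper values for each assumed delay, because the earlier study used the same criterion and its SD may already contain this noise.

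**6. The two descriptions of the criterion.** Intervention and Number of patients needed require more than 5 s at or below 50. Data collection and data management has no such duration. Five seconds is 0.0083 mg/kg, or 28% of the planned difference. A discrepancy applied equally to both groups would cancel, but the sections should be reconciled so that one rule defines the endpoint.

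**The case against.** The case against is substantial, and several parts of it stand.

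- **The caller is blinded.** The person who determines the endpoint and records the dose does not know the group and is in another room. Call delay is then plausibly equal in the two groups and cancels. This stands, and it confines the concern to the step from call to stop.
- **No evidence of a differential delay.** The article does not say who stops the pump or that anyone stops it sooner in jaundiced patients. This also stands. The seconds in the table are assumptions and show sensitivity, not an observed bias.
- **Dose to pump stop is not the only reading.** Data collection and data management describes the requirement up to a BIS value. That wording is compatible with a dose-to-criterion endpoint, but the article gives no means of deriving one. Intervention and Assessment of primary endpoint both pair the dose with the start-to-end infusion time, so dose to pump stop remains the more natural reading.
- **Random delay is small.** An added SD of 5 s moves the requirement only from 29 to 31 per group, and 32 are planned. This stands.

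A reader might infer three stronger claims that the documents do not support:

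- **That the endpoint cannot be checked.** The list of electronically recorded signals is open-ended and covers pulmonary and cardiovascular signs, and BIS is neither. Its absence does not show that the trace is not stored, and a condensed article may leave such detail to the full protocol.
- **That differences between centers in delay and group mix bias the result.** Nothing in the article indicates that either differs by center.
- **That the sample size is wrong on this account.** It is not.

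**Conclusion.** The concern holds in a limited form. As written, the primary value most naturally includes the time from call to pump stop, and that step takes place where group is visible. A delay equal in both groups does no harm. A delay that differed by group would enter the result on a scale where the whole planned effect is 18 s: an assumed 3, 5 or 10 s would be 17%, 28% or 56% of it. With no true difference, 5 s would raise the rejection rate from 5% to about 12%.

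This rests on the reading of Intervention set out above, on the stated infusion rate and planning means, and on delays for which the article gives no figure. The article provides for no stored BIS trace and no later verification of the call, and whether a trace exists is unknown. It is a worthwhile improvement to the measurement, not a demonstrated bias.

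**What to change.** 1. Record BIS and the infusion start electronically, with time stamps.
2. Derive the primary endpoint afterwards, by one fixed rule applied without knowledge of group: infusion rate × time from start to the first moment at which BIS has been at or below 50 for more than 5 s. This matches Number of patients needed and Intervention.
3. Reconcile the wording in Data collection and data management with that rule.
4. Keep the dose at pump stop as a secondary value and as the fallback for patients without a usable trace. Report how many patients in each group rely on the fallback, because the stop delay remains in their values.
5. State how the call is passed to the operating room and who stops the pump.

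This changes the measurement only, not the treatment.

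The cost is data handling at three centers. BIS is already viewed over the LAN, so no extra staff or patient procedure is needed, although the article does not confirm that the signal can be exported. Enrollment began on 1 March 2021, so patients already treated may have no trace, which is why the fallback is needed. The derived value may also differ slightly from how the requirement was measured in the earlier study behind the sample size.

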### Primary objective

#### Definition of primary endpoint

The primary endpoint of the study—reflecting the change of sensitivity of remimazolam in patients with obstructive jaundice—is remimazolam requirement with BIS of 50 as the endpoint.

#### Assessment of primary endpoint

We will record the requirement of remimazolam and the time interval between the start and end of the infusion.

### Secondary objectives

#### Definition of secondary endpoints

Secondary endpoints focus on hemodynamic stability and safety, which is reflected in the number of cardiovascular events and the average percent change to baseline in the mean arterial pressure and heart rate.

#### Assessment of secondary endpoint

Hemodynamic data at the designated time points will be recorded during the perintubation period.

### Safety management and adverse event

Researchers make sure that emergency equipment is working throughout the process. An adverse event refers to any untoward medical occurrence which happens during the trial. Adverse events include but are not limited to respiratory depression or cardiocirculatory instability. All adverse events will be treated immediately. If spontaneous ventilation is insufficient (SpO_2_ < 92%), auxiliary mask ventilation is given to the patients when necessary to maintain ETCO_2_ between 34 and 45 mmHg. Cardiovascular events should be handled promptly, with 5–15 mg ephedrine given if the patient’s blood pressure is below 60 mmHg and 5 mg atropine given if the patient’s heart rate is below 50 bpm. The type of adverse event, likely cause, and treatment will be documented and discussed in data monitoring committee (DMC) meetings.

### Data collection and data management

Before surgery, general information and the surgical methods of the patients are investigated, and indexes such as TBL, bile acid, albumin, alanine aminotransferase (ALT), aspartate aminotransferase (AST), and alkaline phosphatase (ALP) are recorded. The requirement of remimazolam until the patient’s BIS value reaches 50 and the time interval from the start to the end of infusion are recorded. Pulmonary and cardiovascular vital signs are recorded electronically throughout the procedure, including SpO_2_ measured by a pulse oximeter, HR, IBP, RR, and ETCO_2_. Data will be collected on paper case report forms (CRFs) by an anesthesiologist assistant blinded to the group allocation in each center.

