Hyperbilirubinemia has been well-described to have toxic effects on the brain. Histologic evidence of neurologic damage in the brain, such as atrophy and pyknosis of nerve cells, ghost cells, and neuronophagia, was observed in a well-designed canine model of cholestasis secondary to bile duct resection. Furthermore, neurologic damage is more widespread as the duration of hyperbilirubinemia is prolonged [19]. It has been reported that interaction of unconjugated bilirubin with synaptosomal membrane vesicles results in oxidative injury, calcium intrusion, and loss of membrane asymmetry and functionality, thus potentially contributing to the pathogenesis of encephalopathy by hyperbilirubinemia [20]. Acute hyperbilirubinemia results in presynaptic neurodegeneration at a central glutamatergic synapse [21]. Unconjugated bilirubin could also impair the release and uptake of the neurotransmitter glutamate, indicating possible excitotoxic damage [22, 23]. It has been reported that altered neurotransmission could occur in the brains of cholestatic patients. Some evidence suggests that fatigue and pruritus accompanying with cholestasis may be the consequences of a central mechanism, increased opioidergic neurotransmission [24, 25], and defective serotoninergic neurotransmission [26–28]. Consequently, all these changes in patients with obstructive jaundice may, at least in part, induce the increased sensitivity to anesthetics and the reduction of anesthetic requirements.

Our previous study demonstrates that the MACawake of desflurane was significantly decreased in obstructive jaundice patients compared with non-jaundiced controls; furthermore, there is a highly inverse relation between the MACawake of desflurane and the concentration of serum total bilirubin [29]. We also demonstrated that patients with obstructive jaundice had an increased sensitivity to isoflurane, more bradycardia and hypotension during anesthesia induction and maintenance, and a prolonged recovery time compared with non-jaundiced patients [30].

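### Dose to a fixed BIS of 50 is read as drug sensitivity, but the article lists no awake BIS and neither stated analysis uses it

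*Protocol article*

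**What the plan says.** Definition of primary endpoint states that the endpoint "is remimazolam requirement with BIS of 50 as the endpoint" and describes it as "reflecting the change of sensitivity of remimazolam in patients with obstructive jaundice". Under Intervention, the sensor is placed before the infusion ("Apply the BIS sensor (BIS™XP sensor) as recommended by the manufacturer"), and remimazolam runs at 6 mg/kg/h "until the BIS is ≤ 50 longer than 5 s". An assistant in the next room "observes the vital signs and BIS values in the next room via the LAN, determines the endpoint of titration, and records the dosage of remimazolam" and the infusion time.

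The data taken from the titration are named in three places: Intervention, Assessment of primary endpoint, and Data collection and data management. Each names dose and infusion time. The last says that the dose until the "BIS value reaches 50 and the time interval from the start to the end of infusion are recorded". Cardiovascular and pulmonary signs "are recorded electronically throughout the procedure, including SpO" and a few others; BIS is not among those named. Change from baseline is mentioned only for arterial pressure and heart rate, under Definition of secondary endpoints.

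Allocation and allocation concealment assigns patients to groups by total bilirubin. Statistical analysis plans a t test or rank-sum test between groups, and a multiple regression of dose on TBL, TBA, ALB, AST and ALT.

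**The concern.** The dose needed to reach a fixed threshold depends on two things: how far BIS has to fall, and how much it falls per mg/kg. Only the second is sensitivity to the drug. The stated group test does not separate them. Nor does the regression, because an association between bilirubin and dose could arise through the starting BIS as well as through sensitivity.

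The groups are not randomised, so nothing in the design balances the starting value. The Discussion argues that "Hyperbilirubinemia has been well-described to have toxic effects on the brain" and that neurotransmission is altered in cholestasis. Effects of that kind would be present before any drug is given. If they lowered awake BIS, the titration would be shorter in the jaundiced group at equal drug sensitivity. The error would run in the direction of the hypothesis, and the trial's conclusion is meant to inform dosing in these patients.

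**Working it through.** **Inputs from the article.** Number of patients needed: means 0.13 and 0.16 mg/kg, SD 0.04 in both groups, α = 0.05, power 0.8, 29 per group before dropout. Intervention: 6 mg/kg/h, threshold BIS 50.

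**Assumptions, not in the article.** Awake BIS of 97 in controls (90 as an alternative); a gap of 3 to 5 points (9 as an extreme); the shape of the BIS response; equal drug sensitivity in both groups.

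1. *The plan's own figure.* ES = 0.03/0.04 = 0.75, and n = 15.7/0.75² + 1 = 28.9, so 29. A two-sided t test with 29 per group has 80.1% power. The figure reproduces, and this point does not change it.

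2. *Time scale.* 6/3600 = 0.00167 mg/kg/s. The planning means correspond to 0.16/0.00167 = 96 s and 0.13/0.00167 = 78 s, which are 18 s apart.

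3. *Linear fall.* 97 − 50 = 47 points over 0.16 mg/kg gives 0.0034 mg/kg per point. A start 3 points lower saves 0.0102 mg/kg (about 6 s), and 0.0102/0.03 = 34% of the planned difference. A start 5 points lower saves 0.0170 mg/kg (about 10 s), or 57%. The whole 0.03 mg/kg needs a gap of 8.8 points. With an awake BIS of 90 the rate is 0.16/40 = 0.004 mg/kg per point: 0.012 (40%) and 0.020 (67%), and 7.5 points for the whole difference.

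4. *Lag of 48 s, then linear.* 47 points in the remaining 48 s is 0.98 points/s. Three points take 3.1 s, or 0.0051 mg/kg (17%). Five points take 5.1 s, or 0.0085 mg/kg (28%).

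5. *Sigmoid response.* With BIS = E0/(1 + (D/D50)^γ), the dose to BIS 50 is proportional to (E0 − 50)^(1/γ). The saving for a gap of k points is 0.16 × [1 − ((47 − k)/47)^(1/γ)]. For 3 and 5 points:
   - γ = 2: 0.0052 (17%) and 0.0087 (29%)
   - γ = 3: 0.0035 (12%) and 0.0059 (20%)

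6. *Chance of a significant group difference at equal sensitivity.* This uses 29 per group, SD 0.04, a noncentral t distribution with noncentrality d/(0.04 × √(2/29)) = d/0.0105, and an awake BIS of 97 in controls.

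| Gap in awake BIS | Linear | γ = 2 | γ = 3 |
|---|---|---|---|
| 3 points | 16% | 8% | 6% |
| 5 points | 36% | 13% | 9% |
| 9 points | 82% | 33% | 18% |

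The nominal rate is 5%. These rates are errors about *sensitivity*. In each scenario the dose *requirement* does differ between the groups.

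**The case against.** A reader might infer that awake BIS is not recorded and that the question could never be checked afterwards. The article does not support this. It condenses a fuller protocol, its list of electronically recorded signs is open, BIS is watched throughout the titration, and Figure 1, the schedule of assessments, is not shown. What stands is that the text names no awake BIS.

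A reader might also infer that jaundiced patients do start lower. No section says so. The Discussion cites animal and cellular findings, fatigue and pruritus as reasons for greater anaesthetic sensitivity, not as evidence of a depressed awake EEG index. Several provisions also limit gross imbalance. Patients sign consent on the day of surgery. ASA IV and V, psychiatric history, known or suspected metabolic disease, and analgesic or neuromodulating drugs are excluded. No one is premedicated, and all lie with eyes closed and covered. A subclinical difference remains possible but undocumented.

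A third inference would be that a dose difference counts only if it survives adjustment. That goes too far. If jaundice lowers awake BIS, the value lies on the pathway from jaundice to requirement, and conditioning on it can remove part of a real effect. Whether jaundiced patients need less drug is a valid question without adjustment.

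Finally, covariates for supporting analyses are often left to an analysis plan, and none is shown. That is fair. However, the article does state its group test and does name its regression covariates. As stated, they cannot support the specific reading of the endpoint as sensitivity.

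**Conclusion.** The point holds as a limit on interpretation, not as a demonstrated bias. The stated analyses can show a difference in dose requirement. They cannot show that the difference is one of sensitivity to remimazolam, because starting BIS enters neither of them and the groups are not randomised.

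If a 3 to 5 point gap in awake BIS existed, the calculations with an awake BIS of 97 put its contribution between 12% and 57% of the planned difference, depending mainly on the response curve. The awake BIS, the gap and the curve are all assumptions. Only a gap of about 9 points on a linear curve would account for the whole planned difference. The remedy is nearly free and bears directly on the trial's own question, so it is worth making.

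**What to change.** - In Data collection and data management, state that awake BIS is recorded immediately before the infusion from the sensor already applied, and that it is reported by group.
- In Statistical analysis, keep the unadjusted group comparison as primary. Add a pre-specified supportive comparison of dose between groups with awake BIS as a covariate, and report both.
- Interpret the unadjusted result as the difference in dose requirement. If it shrinks materially after adjustment, qualify the claim of increased sensitivity, and note that awake BIS may itself be an effect of jaundice.

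The cost is one field on the case report form and one model degree of freedom. The sample size and procedures do not change.
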